### Risk groups and development of the predictive screening tool

The predictive model will be used to develop a risk stratification tool to inform an individual’s absolute risk of poor outcome. The stratification tool will inform clinical decision-making for precision rehabilitation. Items will be selected for the model if they are statistically significantly (P<0.05) associated with poor outcome in the logistic regression analysis, and those deemed clinically important to retain using expert opinion (regardless of statistical significance, study steering group) to improve face validity for clinicians and avoid overfitting of the model.^37^ The regression model with included predictive factors will be fitted to the data from the first of the two cohorts to obtain a final set of parameter estimates (i.e. alpha and beta terms), which will be used to form the model. An important requirement of the stratification tool is that it should be sufficiently brief to facilitate use in clinical practice. Thus, we will look to simplify the model where possible to facilitate its use, but without important reduction in its predictive ability in terms of calibration and discrimination. For example, if multi-item questionnaire scores are included in the model, then we will evaluate whether just one of the questionnaire items is sufficient. Ideally, this process will result in a full and simplified model.

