### Objectives

(1) Identify predictive factors for poor outcome (chronic pain and disability at 6 months postinjury) following acute musculoskeletal trauma. (2) Develop a predictive model to inform a screening tool to identify the predicted risk of poor recovery (transition from acute post-traumatic pain to chronic pain and disability). (3) Estimate the predictive performance of the screening tool through validation of the model in a separate dataset. (4) Document the clinical course of symptoms at 3 and 12 months following acute musculoskeletal trauma.

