### Sample size

In predictive modelling, a larger sample size enables lower bias and variance, and permits the prospective prediction of new observations.^15^ The number of predictors will be reduced using exploratory factor analysis. This process will ensure that the sample size provides at least 10 cases per candidate predictor, to adequately power the final regression analysis.^35 36^ Data will be collected for an estimated 300 participants per cohort (n=600 total) to allow for withdrawals (primarily expected deaths within the first 3 months) and losses to follow-up, so that final data are available for 250 participants per cohort (n=500 total).

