### Statistical analysis methods and management of missing data

For each cohort, potentially eligible patients, numbers examined for eligibility, confirmed eligible, recruited into the study, completing follow-up and analysed will be reported in a flow diagram. Reasons for non-participation, exclusion, drop-outs and withdrawal (eg, death) will be reported at each stage. Participant characteristics will be descriptively presented. For each variable of interest, the number of participants with missing data will be reported.

For the first cohort to develop the predictive model, an initial exploratory data analysis stage will summarise the data.^15^ Correlations between candidate predictive factors will be calculated at baseline. Outcome (CPGS) scores will be dichotomised into good and poor categories as described previously. Data reduction will use exploratory factor analysis to assess factor loading of candidate predictors (summary scores) on poor outcome at 6 months. This will enable the number of candidate predictors entered into the final model to be reduced to 25, which can be supported by the cohort sample of 250. This process reduces the risk of over-fitting the model and the risk of selecting the wrong variables due to correlation between predictor variables (multicollinearity).^37^

Statistical modelling for prediction has been planned *a priori*. To explore the influence of each predictive factor on poor outcome at 6 months, a logistic multivariable regression model will be fitted to the dichotomised outcome scores to calculate low and high risk of poor outcome. Odds ratios for each candidate predictive factor will be reported, adjusted for other factors and account for clustering (eg, level of injury severity). If necessary, multiple imputation^38^ will be used to deal with missing outcome data. The characteristics of those patients with and without 6-month data will also be compared, to inform whether patients with no 6-month data were missing at random. Reduced multivariable analyses will be considered if necessary (eg, removing one of two candidate predictive factors that are highly correlated at baseline), to examine the robustness of the conclusions.

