### Development versus validation

For validation of the model, data from the second of the two cohorts will be compared with that of the first to enable analysis of the distribution of important variables, inclusive of demographic, predictor and outcome variables. The predictive performance of the screening tool (discrimination, calibration and goodness of fit) will be assessed using data from the second cohort. Data in both cohorts will be consistent in terms of setting, eligibility criteria, outcome and predictors.

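### Predictive factors (Objective 1) are selected at P<0.05 among 25 candidates in cohort 1, and no factor is then estimated in data that did not select it

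*Protocol article*

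**What the plan says.** The Objectives section lists factor identification first and separately from building and validating the tool: "Identify predictive factors for poor outcome (chronic pain and disability at 6 months postinjury) following acute musculoskeletal trauma".

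Under Statistical analysis methods, data reduction precedes the regression: "This will enable the number of candidate predictors entered into the final model to be reduced to 25". Adjusted odds ratios will be reported for every candidate, but no rule is attached for calling a candidate predictive.

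The section on risk groups and the screening tool gives two routes into the model. One is statistical: "Items will be selected for the model if they are statistically significantly (P<0.05) associated with poor outcome in the logistic regression analysis". The other is judgement: "those deemed clinically important to retain using expert opinion (regardless of statistical significance, study steering group". The coefficients come from the first cohort.

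Development versus validation gives the second cohort two uses. One is a comparison of variable distributions between cohorts. The other is the performance of the tool: "The predictive performance of the screening tool (discrimination, calibration and goodness of fit) will be assessed using data from the second cohort".

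**The concern.** The selection rule is written for model items (Objective 2). It also serves Objective 1, because the article states no other criterion that picks out factors. That has two consequences.

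First, 25 tests at the 5% level in one cohort will usually let through at least one candidate that predicts nothing. Validation of the tool need not reveal this, because a tool with several true items and one or two noise items can still discriminate well in cohort 2.

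Second, a factor that passes a threshold in the data used to estimate it has, on average, an exaggerated odds ratio. Fitting 25 terms to 250 patients exaggerates it further. The reader of the factor list would see only those estimates.

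The list is meant to be used: the Discussion says that identifying factors will help to target interventions. The analysis section itself names the selection of wrong variables as a risk, but treats it only as a matter of correlated predictors.

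**Working it through.** **Inputs from the protocol article.** 250 analysed participants per cohort and at least 10 per candidate predictor (Sample size); 25 candidates in one multivariable logistic model (Statistical analysis methods); P<0.05 per item (Risk groups section).

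**Assumed, because the article gives no figure.** Two-sided Wald tests; normally distributed candidates; poor-outcome rates of 30 to 70%; common correlation between candidates of 0 to 0.6; the number of true factors and their odds ratios.

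**The plan's own figure.** 250 / 10 = 25 candidates. It reproduces.

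**Benchmark with independent tests and no true factor.**
- Chance of at least one selected: 1 − 0.95^25 = 0.723, or 72%.
- Expected number: 25 × 0.05 = 1.25.

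**Simulation of the planned model with no true factor** (n=250, 25 candidates).
- At least one is selected in 76.6 to 77.8% of runs across outcome rates of 30, 50 and 70% and correlations of 0, 0.3 and 0.6. A longer check of 8000 runs gave 78.1%.
- About 1.5 are selected on average.
- The excess over 72% is a small-sample effect: at n=2500 the simulation gives 71%.
- With fewer candidates the figure falls: 69% with 20, 57% with 15, 43% with 10.

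**The more realistic case: 5 true factors and 20 null ones.**
- Independent tests on the 20 null candidates: 1 − 0.95^20 = 0.642, or 64%.
- Simulation of the planned model (odds ratio 1.5 or 2.0 per SD, outcome rate 30 or 50%, correlation 0 or 0.3): at least one null factor is selected about 70% of the time (68 to 73% across the runs made). The mean is 1.2 to 1.4.
- Per null candidate: 1.22/20 = 6.1% to 1.37/20 = 6.9%, against the nominal 5%.

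**Size of the selected odds ratios** (true odds ratio 1.5 per SD, uncorrelated candidates).
- True log odds ratio: ln 1.5 = 0.41.
- Mean among true factors selected in cohort 1: 0.52 to 0.54, that is e^0.52 = 1.68 to e^0.54 = 1.72.
- Mean of the same factors refitted in cohort 2: 0.41, that is an odds ratio of about 1.5.

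When candidates are correlated, the cohort 2 model is still free of cohort 1 selection. Its odds ratios are adjusted only for the items refitted, however, so they also carry part of the effect of any correlated true factor that was not selected.

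**The case against.** **The rule is about model items.** The section heading and the sentence concern the tool. The analysis section describes exploring the influence of each factor and reports every odds ratio, and Table 2 promises that all results will be reported. No sentence says that P<0.05 makes a factor identified. This stands as a limit on wording: the rule governs Objective 1 only by default. A fuller protocol or analysis plan might add a reporting rule. The point does not rest on that gap alone, because the article does state the threshold, the number of candidates and what cohort 2 is for, and that stated use contains no factor-level estimate.

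**The all-null case is unrealistic.** A reader might infer that the study will name factors about 77% of the time although nothing predicts. The documents do not support that as an expectation. The Introduction cites psychosocial variables as known predictors, and candidates were chosen for a theoretical association with chronic pain. The 77% is a benchmark for exactly 25 candidates. The case with some true factors is the relevant one, and its figure is still about 70%.

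**Familywise control is not promised.** Among null candidates the error is 6 to 7% each, not far from what P<0.05 conveys. That is fair, and the article claims no familywise rate. It is a reason not to demand a second significance threshold. It does not answer the exaggerated odds ratios or the absence of any independent estimate.

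**Expert opinion.** A reader might infer that the steering group's items ignore the data. The text says only that significance is not required. The group may look at odds ratios and intervals, and the stated aims are face validity and less overfitting. What remains is that such items should be labelled.

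**Conclusion.** The point holds as a cheap and worthwhile improvement to how Objective 1 is concluded. As stated, factors are selected and estimated in the same 250 participants, and cohort 2 is not used to estimate any of them. With 25 candidates of which 5 are real at an odds ratio of 1.5 to 2.0 per SD, the selected set contains at least one null factor about 70% of the time. For uncorrelated candidates, a true odds ratio of 1.5 appears as about 1.7 once selected. These sizes rest on assumed outcome rates, correlations, effect sizes and normally distributed candidates, and the chance of a null factor being selected falls if fewer than 25 candidates are entered.

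A reader might go further and conclude that the screening tool or its validation is unsound for this reason. The documents do not support that: the second cohort tests the tool as a whole, which is what Objective 3 requires.

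**What to change.** Add to Development versus validation: *After the tool has been frozen and validated, the selected items of the full model will be refitted together in cohort 2. Each factor's cohort 2 odds ratio and 95% CI will be reported beside its cohort 1 estimate. The conclusion for Objective 1 will be based on the cohort 2 estimates. Items supported by cohort 1 alone will be described as candidate factors, and items retained by expert opinion will be labelled as such.*

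A second P<0.05 threshold in cohort 2, in the same direction, is optional and not required. In simulation with 5 true factors it cuts the chance of any false factor to 3 to 9%. It also lowers detection of a true factor at odds ratio 1.5 from 60–82% to 48–68%. That trade-off is for the study team to judge.

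The cost is one extra logistic model and a few lines of text. The article already says that both cohorts share predictors and outcome, so no patients or procedures are added. Weaker true factors may be reported with less certainty.

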
Criteria^42^	Methodological decisions to improve quality
Study design	
Inception cohort	Clear description of population Clear description of the participants at baseline
Source population	Clear description of population Clear description of sampling frame and recruitment (method and timing)
Inclusion and exclusion criteria	Clarity of eligibility criteria
Prospective design	Clarity of study design
Study attrition	
Number of drop-outs	Adequate participation rate Clear description of attempts to collect information on participants who dropped out Reporting numbers and reasons for loss to follow-up
Information provided on method of management of missing data	Appropriate methods of imputation of missing data
Predictive factors	
All predictive factors described used to develop the model	Clear definition of predictive factors An adequate proportion of participants has complete data for the predictive factor
Standardised or valid measurements	The measurement of the predictive factor is reliable and valid The measurement of the predictive factor is the same for all participants
Linearity assumption studied	Linearity of data will be reported
No dichotomisation of predictive variables	Continuous variables will be reported where possible
Data presentation all predictive factors	Complete data will be presented
Outcome measures	
Description of outcome measures	The outcome is clearly defined
Standardised or valid measurements	The measurement of the outcome is reliable and valid The measurement of the outcome is the same for all participants
Data presentation of most important outcome measures	Complete data will be presented
Analysis	
Presentation of univariate crude estimates	An appropriate strategy for model building is described An adequate statistical model described
Sufficient numbers of subjects per variable	Adequate data will be presented
Selection method of variables explained	Sufficient data will be presented to enable assessment of the adequacy of the analytic strategy All results will be reported
Presentation of multivariate estimates	An appropriate strategy for model building is described An adequate statistical model described
Clinical performance/validity	
Clinical performance	Clinical performance of the model will be reported
Internal validation	Internal validation will be reported
External validation	Not a focus of this study

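### Selecting predictors at P<0.05 and refitting them unshrunk in the same cohort does not avoid overfitting, and cohort 2 as planned would reveal this but not correct it

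*Protocol article*

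**What the plan says.** Three steps are fixed in the protocol article, under the heading on risk groups and development of the predictive screening tool.

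- **Selection.** "Items will be selected for the model if they are statistically significantly (P<0.05) associated with poor outcome in the logistic regression analysis". A second route admits "those deemed clinically important to retain using expert opinion (regardless of statistical significance, study steering group"). The stated purpose is "to improve face validity for clinicians and avoid overfitting of the model".
- **Estimation.** The model with the selected factors "will be fitted to the data from the first of the two cohorts to obtain a final set of parameter estimates", and these alpha and beta terms form the model. No shrinkage, penalty or optimism correction is named.
- **Simplification.** The tool may be shortened "without important reduction in its predictive ability in terms of calibration and discrimination". The data set, the calibration measure and the size of an important loss are not given.

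The statistical analysis section sets the number of candidates entering the regression: "reduced to 25, which can be supported by the cohort sample of 250". The section on development versus validation assesses discrimination, calibration and goodness of fit in the second cohort. Table 2 states "Internal validation will be reported" and says external validation is not a focus.

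**The concern.** Choosing predictors by significance and then estimating their coefficients in the same data favours predictors whose estimates happen to be large in that sample. An unshrunk refit carries this excess into the final coefficients. The step is nevertheless presented as a guard against overfitting.

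The tool is meant to give an individual's absolute risk and to steer rehabilitation decisions. If its coefficients are too large, high risks are overstated and low risks understated. Ranking of patients also falls short of what the development data suggest. The text provides for no updating of the coefficients after validation, so the fault would come to light only when both cohorts had been used.

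**Working it through.** **Inputs.** From the protocol article: 25 candidates, 250 analysed and 300 recruited per cohort, selection at P<0.05, refit in cohort 1. Not in the documents, hence assumed: a two-sided Wald test, an outcome rate of 30% or 50%, and the number, size and correlation of true effects.

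**1. The plan's own figure.** 25 × 10 = 250, and 300 × (1 − 1/6) = 250. The figure reproduces only if a case means a participant. For a binary outcome the smaller class limits the information. It is at most 250/2 = 125, so at most 125/25 = 5 per candidate. At a 30% outcome rate it is 75/25 = 3.

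**2. Chance selections.** If all 25 candidates were null and independent, 25 × 0.05 = 1.25 would be selected on average, and 1 − 0.95^25 = 0.72 is the chance of at least one. In simulated pure noise, 1.5 to 1.6 were selected on average. Apparent C was about 0.61 to 0.62 against a true 0.50.

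**3. Selection and refit with true predictors.** Each run used n = 250 and 25 normal candidates, fitted the full logistic model, kept those with P<0.05 and refitted by maximum likelihood. Performance was then measured in 20,000 new subjects (200 runs per scenario). Cells give the 30% / 50% outcome rate.

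| True predictors; log-OR per SD; correlation | New-data slope, selected | New-data slope, all 25 | C selected, apparent → new | C all 25, new |
|---|---|---|---|---|
| 5; 0.5; 0 | 0.725 / 0.743 | 0.526 / 0.559 | 0.785→0.726 / 0.779→0.726 | 0.711 / 0.709 |
| 5; 0.5; 0.3 | 0.789 / 0.808 | 0.615 / 0.641 | 0.844→0.803 / 0.838→0.803 | 0.796 / 0.795 |
| 10; 0.3; 0 | 0.588 / 0.603 | 0.530 / 0.538 | 0.742→0.658 / 0.743→0.664 | 0.688 / 0.685 |
| 10; 0.3; 0.3 | 0.710 / 0.724 | 0.617 / 0.641 | 0.843→0.782 / 0.839→0.784 | 0.813 / 0.811 |
| 25; 0.1; 0.3 | 0.691 / 0.721 | 0.586 / 0.640 | 0.784→0.715 / 0.774→0.713 | 0.762 / 0.766 |
| 25; 0.2; 0 | 0.411 / 0.430 | 0.488 / 0.523 | 0.745→0.618 / 0.739→0.619 | 0.683 / 0.684 |

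The slope of the selected model is 0.41 to 0.81 where 1 is ideal. The loss of C runs from 0.838 − 0.803 = 0.035 to 0.745 − 0.618 = 0.127. The selected model is better calibrated than the unselected one in 10 of 12 scenarios and worse in 2.

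To illustrate, take a slope of 0.6 with risks centred at 50%. A stated risk of 80% has log odds ln(0.8/0.2) = 1.386. The actual log odds are 0.6 × 1.386 = 0.832, a risk of about 70%.

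**4. Does the proposed change help?** A further setting had 8 true predictors among 25, correlation 0.3, and outcome rates of 30% to 50%.

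| Method | New-data slope | New-data C |
|---|---|---|
| P<0.05, refit | 0.56–0.73 (median) | 0.62–0.71 (apparent 0.69–0.76) |
| All 25, unshrunk | 0.42–0.61 | 0.64–0.73 |
| Cross-validated ridge | about 1.1–1.2 | 0.68–0.76 |

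Here the unselected fit ranks patients better than the selected one by about 0.02 in C. In the step 3 scenarios that difference varies, from 0.017 lower (0.709 − 0.726) to 0.065 higher (0.683 − 0.618). Ridge errs slightly the other way on slope, with risks a little too moderate.

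**5. The simplification criterion.** The maximum-likelihood equations, Σ(y − p) = 0 and Σx(y − p) = 0, force an intercept of 0 and a slope of 1 when the outcome is regressed on the fitted linear predictor in the same data. The simulated apparent slope was 1.0000 in every run, even after cutting to one predictor. Other checks are not empty. A Hosmer-Lemeshow test in the development data rejected 82% of one-predictor models with a missed threshold effect, 93% with a missed U-shape, and 4% of correct ones.

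**The case against.** Several stronger readings are tempting, and the documents do not support them.

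- **That the P<0.05 rule causes the overfitting.** Much of it comes from entering 25 candidates on 250 participants. Selection usually reduced miscalibration compared with the unselected fit. What stands is that it does not remove it.
- **That the simplification check cannot fail.** This holds only for slope and intercept, measured in cohort 1 after a refit. The text names neither data set nor measure, other calibration checks can fail there, and discrimination must be preserved as well.
- **That the promised internal validation is missing.** With external validation declared out of focus, Table 2 may well mean the second cohort, which shares setting, eligibility, outcome and predictors. A resampling method could also be left to a fuller document.
- **That expert items are picked after the results are seen.** No timing is given. The group could name them in advance.
- **That the overfitting clause describes the P<0.05 rule.** It follows both routes and may refer to expert opinion alone. Adding non-significant terms does not reduce overfitting either, so the claim is unsupported on both readings.
- **That objective 1 fails.** The statistical analysis section reports adjusted odds ratios for every candidate, so identifying predictive factors does not rest on the screen alone.

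Two further points are fair. The simulations omit the factor-analysis reduction and the expert-retained items, so they show direction and rough size, not a forecast. The second cohort would reveal the optimism before the tool's performance is reported. However, nothing in the text provides for recalibration, and the cohort 1 estimates are described as final. Adding shrinkage would therefore change published text, not fill in a detail left to an analysis plan.

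**Conclusion.** The concern holds in a limited form. The stated procedure does not avoid overfitting, and its coefficients would give absolute risks that are too extreme. The ceiling of 5 per candidate follows from the plan's own figures at any outcome rate. The calibration slope of about 0.4 to 0.8 and the loss in C of roughly 0.04 to 0.13 depend on the assumed outcome rates and effects, but the direction was the same in all 12 scenarios with true predictors. Selection shares the blame with the ratio of candidates to participants. Cohort 2 serves as a detector, not a remedy. The simplification rule needs a stated data set and measure: apparent slope and intercept in cohort 1 carry no information, while choosing the short form in cohort 2 would end that cohort's role as independent validation of it.

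**What to change.** - Replace P<0.05 selection and the unshrunk refit with penalised logistic regression on the capped predictor set, or with a full model and a bootstrap-estimated uniform shrinkage factor.
- Have the steering group name the clinically mandatory items before outcome data are analysed.
- Bootstrap the whole process of reduction, selection and simplification in cohort 1.
- Judge the simplified model on optimism-corrected C and calibration slope in cohort 1, and keep cohort 2 for validating the finished full and simplified models.
- Delete the claim that the present rule avoids overfitting.

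The cost is more analysis work, possibly software beyond the basic SPSS menus, and less favourable reported development performance. No further patients or data collection are needed.
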